**Methods/design:**

This is a double-blind, randomized controlled trial. A total of 156 patients are randomly assigned to: G1, 5 Hz TEAS; G2, 100 Hz TEAS; G3, mixed TEAS (alternative use of daily 5 Hz and 100 Hz TEAS) and G4, placebo TEAS. In the G1, G2 and G3 groups, TEAS is conducted at acupoints SP9 and GB34 of the leg that was operated on (at a wave of continuous, balanced and asymmetrical biphasic square, with a pulse width of 200 μs, and a strong but comfortable current) for 30 min prior to a 30-min rehabilitation session per day for 2 weeks. In G4 group, TEAS is delivered at a strong but comfortable current for 30 s, then the current is gradually decreased to none over the next 15 s. The primary outcomes are measured before surgery, at baseline (POD 3, before TEAS intervention), week 1 and 2 after TEAS intervention with the Numeric Pain Rating Scale and The American Knee Society Score. The secondary outcomes include: (1) Active range of motion of the knee that was operated on; (2) Surface electromyography of both quadriceps; (3) Modified 30-s sit to stand test; (4) Additional usage of analgesia; and (5) SF-36. The additional outcomes include: (1) Patients’ satisfaction rate; (2) Patient’s expectation rate; and (3) Incidence of analgesia-related side effects. To test the blinding of participants and assessors, they are asked to guess whether the subjects received active or placebo TEAS within 5 min after the latest intervention. The safety and financial cost of TEAS are assessed.

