### Sample size

The sample size will be calculated using pain ratings from the previous studies [27–29]. The formula:$$ n=\frac{2{\left({Z}_{\alpha }+{Z}_{1-\beta}\right)}^2{\sigma}^2}{\Delta ^2} $$

An effect size (△) of 2 with a standard deviation (SD) of 2.88 between low-frequency (LF) TEAS and placebo-TEAS (*n* = 33 × 4/0.85 = 156), an △ of 2.35 with a SD of 2.56 between high-frequency (HF) TEAS and placebo-TEAS (*n* = 19 × 4/0.85 = 95), an △ of 1.1 with a SD of 0.7 between mixed TEAS and placebo-TEAS (*n* = 7 × 4/0.85 = 35) [26]. Using this information, a four-group study will be established: 33 patients in each group, α = 0.05 (two-sided), β = 0.2 (80% power) [30]. Considering a possible sample loss of 15%, the final sample size will be set with 39 patients in each group.

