### Randomisation and allocation concealment

Participants who meet the screening criteria will be randomized into four balanced groups: G1, G2, G3 and G4. The randomization sequence will be computer-generated by an independent research staff (C) with a 1:1:1:1 ratio using SPSS 21.0.

At POD 3 and before the TEAS application, three physical therapists (D, E, F) will be mainly responsible for the treatment sessions and outcomes evaluation. Initially, D will perform the basic measurements of participants in four groups and double-check whether the sensation in the leg that was operated on is normal. After D leaves the ward, E will apply a 30-min TEAS intervention and subsequently F will perform a 30-min rehabilitation session per day in four groups. One TEAS intervention and one rehabilitation constitute one treatment session. Immediately after the end of one treatment session, D will return to the ward, evaluate and record the outcomes according to the trial design. Researchers except for C and E will be blinded to the treatment allocation. Randomisation and allocation concealment in a light-tight sealed envelope until E firstly reveals the TEAS intervention according to the random number sequence at POD 3. Participants will be required not to communicate with any other researchers, participants and care providers to minimize the risk of potential bias. After the latest TEAS intervention, participants and outcome assessors will be asked to guess whether the subjects received active TEAS or placebo TEAS within 5 min to evaluate the blinding quality.

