### Outcomes evaluations

Pain intensity (rest and movement) and the American Knee Society Score (AKSS) are the primary outcomes. Secondary outcomes include active range of motion (AROM) of the knee that was operated on, surface electromyography of both quadriceps, the modified 30-s sit to stand test, additional use of analgesics and the 36-item Short Form health survey (SF-36). The additional outcomes include patient satisfaction rate, patient expectation rate and the incidence of analgesia-related side effects.

The pain intensity, AROM, incidences of analgesia-related and TEAS-related side effects will be daily recorded. Evaluation of the patient satisfaction rate and patient expectation rate will be conducted after the first episode of the TEAS intervention. The SF-36 will be evaluated at two time points: before the TEAS intervention, and 2 weeks after the TEAS intervention. The assessment time points of the remaining outcomes are before the surgery, after the surgery before the TEAS intervention(at POD 3), and 1 week and 2 weeks after the TEAS intervention.

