### Statistical analysis

All data will be analyzed using the statistical package for IBM SPSS Statistics V21. The intention-to-treat (ITT) and per-protocol sets (PP) will be analyzed. Continuous data are presented as mean ± standard deviation (SD), and categorical variables are described as percentages. Baseline data will be collected and analyzed. Continuous data with normal distribution and homogeneity variance will be analyzed using analysis of variance (ANOVA). Otherwise, the Kruskal-Wallis *H* test will be performed.

Statistical analysis includes the following four aspects. Firstly, the repeated measurement data will be analyzed using the mixed-effects model or generalized estimating equation (GEE) or generalized linear mixed models (GLMMs). Secondly, the correlation between different outcomes will be analyzed using the multiple linear regression or logistic regression. In this study, NRS, sEMG or AROM are independent variables, whereas the AKSS or m30STS test are dependent variables. Psychological factors serve as covariance. Thirdly, the safety analysis of TEAS will be compared between groups using *χ*^2^ test or Fisher’s exact test. Fourthly, health economic evaluation (cost-effectiveness analysis) will be performed. A *P* value < 0.05 (two-side) is considered statistically significant.

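### Three primary measures, two follow-up times and four arms share one unadjusted two-sided 0.05, with no lead outcome, time point or contrast named

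*Protocol article*

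**What the plan says.** Under Outcomes evaluations the article states: "Pain intensity (rest and movement) and the American Knee Society Score (AKSS) are the primary outcomes". That is three measures with equal standing. The abstract adds the timing: "The primary outcomes are measured before surgery, at baseline (POD 3, before TEAS intervention), week 1 and 2 after TEAS intervention". Randomisation is to four arms "with a 1:1:1:1 ratio using SPSS 21.0".

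The Statistical analysis section names ANOVA or Kruskal-Wallis for continuous data and a mixed-effects model, GEE or GLMM for repeated measurements. It closes with one threshold for everything, a P "value < 0.05 (two-side) is considered statistically significant". It does not say which contrast or time point of the repeated-measures model carries the primary conclusion.

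The Sample size section uses "33 patients in each group, α = 0.05 (two-sided), β = 0.2 (80% power". The comparison that sets the number is "An effect size (△) of 2 with a standard deviation (SD) of 2.88 between low-frequency (LF) TEAS and placebo-TEAS". Two other active-versus-placebo pairs are sized separately, each at the same alpha.

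**The concern.** The trial aims to find the best analgesic frequency, and the abstract's Discussion anticipates that mixed stimulation beats placebo, 5 Hz and 100 Hz. Such a conclusion needs several contrasts. With three primary measures and two follow-up times on top, the primary conclusion can be reached by many routes. The one stated rule limits neither their number nor which of them counts.

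At stake is the meaning of a positive result. If any of these routes counts as success at 0.05, the trial's false-positive rate is not 5%. Correcting this also moves the power, because the planned 80% belongs to one unadjusted comparison of two arms.

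**Working it through.** **1. The plan's own figure.** Inputs from Sample size: difference 2, SD 2.88, two-sided alpha 0.05, power 0.80.

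n = 2(1.960 + 0.842)² × 2.88² / 2² = 32.55, so 33 per arm. Then 33/0.85 = 38.8, so 39 per arm and 156 in total. This reproduces the plan. Power at 33 is 80.5%, for one pair at the full 0.05.

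**2. Counting the possible primary tests.** 3 measures × 2 times × 3 placebo contrasts = 18. With all 6 pairs, 3 × 2 × 6 = 36. With one four-group test per measure and time there are 6, and with one time-averaged four-group test per measure there are 3. Two times is a minimum for pain, which is also recorded daily.

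**3. Reference values if tests were independent.** 1 − 0.95^k gives 14.3% for k = 3, 26.5% for 6, 60.3% for 18 and 84.2% for 36. The tests share arms and patients, so these are not the actual rates for pairwise testing.

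**4. Simulation with all four arms equal.** 20,000 trials, 33 per arm, pooled-variance tests at two-sided 0.05. The article gives no correlations, so they were varied. The entries are the chance (%) of at least one significant primary result.

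| Correlation between measures / times | 36 pairwise | 18 vs placebo | 9 vs placebo, time-averaged | 6 omnibus | 3 omnibus, time-averaged |
|---|---|---|---|---|---|
| 0 / 0 | 74.0 | 55.1 | 32.8 | 26.5 | 14.1 |
| 0.2 / 0.5 | 69.8 | 51.6 | 32.4 | 24.8 | 14.5 |
| 0.5 / 0.5 | 65.0 | 47.4 | 29.4 | 22.5 | 12.8 |
| 0.5 / 0.7 | 61.6 | 44.3 | 29.2 | 21.0 | 12.7 |
| 0.7 / 0.7 | 55.1 | 39.1 | 25.9 | 18.6 | 11.4 |
| 0.8 / 0.8 | 47.7 | 33.5 | 23.1 | 15.6 | 10.2 |

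Allowing pairwise tests only after a significant omnibus test at that measure and time leaves the 6-omnibus column unchanged. Even one measure at one time gives about 12% for three placebo contrasts and 20% for six pairs.

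**5. Power under an adjusted test.** For Dunnett with three placebo contrasts and 4 × 32 = 128 degrees of freedom, the critical value is about 2.375. The noncentrality for 5 Hz versus placebo is 2/(2.88 × √(2/33)) = 2.82, so power is about 67%. Adjusting for a baseline that correlates r with the outcome multiplies the SD by √(1 − r²):

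| Assumed r | Noncentrality | Power |
|---|---|---|
| 0.2 | 2.88 | 69% |
| 0.3 | 2.96 | 72% |
| 0.4 | 3.08 | 76% |
| 0.5 | 3.26 | 81% |

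**The case against.** The article lists no set of 36 tests. It names four-group methods and a repeated-measures model, and a statistical analysis plan that is not shown may add a post-hoc procedure. On the methods actually named, the error is about 10–27%. This objection stands against any single headline figure. A reader might infer that the false-claim chance is 55–70%, or that a trial of four equal arms would more likely than not report a winning frequency. The documents do not support that: it needs every pair tested separately at both times on all three measures, with chosen correlations. A significant pair also need not favour an active arm.

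The objection does not remove the point. Three equal primaries, a blanket 0.05 and single-test sizing are positive statements in this document, not gaps left to another one, and an adjustment added elsewhere would change the power basis printed here.

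Nor does an omnibus test settle the trial's own question, because it cannot say which frequency is best. Suppose the three active arms are equally effective and each beats placebo by 2/2.88 = 0.69 SD on every primary measure and time. The omnibus test then usually passes. The simulated chance of at least one false difference between active arms, even after that gate, is about 48% at correlations 0.3/0.5, 37% at 0.7/0.7 and 32% at 0.8/0.8.

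**Conclusion.** The point holds as a missing primary hierarchy with no stated error control. Its size depends on which tests are run, which the article does not fix, and on correlations that it does not give. The lowest value found, about 10%, is still twice the nominal level, so the conclusion does not rest on the most extreme count of tests. It should be corrected before unblinding, because the main conclusion depends on it.

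**What to change.** Name one primary pain measure and one time point, or one repeated-measures contrast, before unblinding. Pain is the natural family because the sample size rests on pain ratings. That section does not favour movement over rest or week 2 over week 1, so the choice is the sponsor's. Make the other measures and times secondary.

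Then state a procedure with strong familywise control at 0.05, for example one of these:
- Holm or Tukey over all six pairs.
- Dunnett for the three placebo contrasts, with active-versus-active contrasts tested (themselves adjusted) only if all three succeed, or labelled exploratory.
- Dunnett-type contrasts of mixed against the other three arms, to match the claim in the abstract's Discussion.

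Opening the active-versus-active tests at full alpha once at least one placebo contrast succeeds is not enough. With Dunnett at the first step, simulated familywise error is about 7.5% when one arm works and 6.8% when two work equally.

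Restate power for the chosen procedure. The change is wording and needs no extra data, since the POD 3 baseline is already collected. The cost is a stated power below 80% for 5 Hz versus placebo unless the baseline correlation is about 0.5 or higher, a value the sponsor would have to justify. Without baseline adjustment, a simple Bonferroni correction for three tests would need 44 evaluable per arm (44/0.85 = 51.8, so 52 per arm and 208 in total). The article assumes no active-versus-active difference, so power for those contrasts cannot be stated until the sponsor supplies one.

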## Discussion

The management of postoperative acute pain remains a challenge. In clinical practice, opioids are essential in the management of postoperative acute pain although multiple opioid-sparing approaches have been developed [48]. However, opioid-related side effects markedly limit therapeutic efficacy and patient satisfaction. Thus, nonpharmacological therapies adjunct to the multimodal analgesic regimen are urgently required [49]. TEAS, a nonpharmacological and noninvasive treatment, is commonly used for the management of postoperative acute pain with fewer adverse effects.

The frequency of TEAS varies from low (LF < 10 Hz) to high frequency (HF > 50 Hz) [21]. The gate control theory and endogenous opioids mechanism are involved in TEAS [20]. The gate control theory explains the analgesic effect of HF stimulation. Compared to LF, HF is more effective in selectively activating large-diameter Aβ afferent sensory fibers and δ opioid receptors in the spinal cord [50] without simultaneously exciting small-diameter C fibers to reduce the transmission of noxious stimuli. HF TEAS exerts a segmental analgesic effect on localizing the specific dermatome with a rapid onset and offset. LF stimulation can be explained by the endogenous-opioid mechanism. LF activates endogenous opioids through stimulating small-diameter Aδ afferent sensory fibers and μ opioid receptors (MORs) [50]. Subsequently, endogenous opiates are released to provide the pain control effect. The analgesic effect of LF is extra-segmental, delayed but lasting. However, repeated electrical stimulation can also lead to opioid tolerance and cross-tolerance equivalent to repeated administration of μ or δ opioid receptor agonists [51]. The separated application of TEAS at 5 Hz and 100 Hz at alternative days may delay the tolerance effect [52, 53].

The frequency of TEAS is a key parameter for the effective management of postoperative acute pain control, while the optimal frequency remains controversial.

In vivo studies [50, 54] have suggested that both LF and HF electrical stimulation provide analgesic effect and strengthen the endogenous analgesic system in experimental animals without side effects. But Xiang et al. [55] revealed that 2-Hz TEAS but not 100-Hz TEAS induced an upregulation of MOR binding potential in numerous pain-related brain areas, and such effects even last until the end of the 2-Hz TEAS intervention in some brain areas. Yu et al. [24] yielded identical results in a rat model that shows that LF TEAS efficiently alleviated the neuropathic pain by regulating the positive expression of MORs in the dorsal root ganglion. In a clinical research, conducted by Huang et al. [26], mixed TEAS considerably reduced the demand for opioids and relieved postoperative acute pain compared to 2 Hz and 100 Hz TEAS alone. One hundred Hz TEAS can decrease the incidence of postoperative nausea and vomiting in patients undergoing video-assisted thoracic surgery. Tokuda et al. [56] also found that compared to a placebo group and a control group, the modulated-frequency electrical stimulation group had a lower pain score at rest and with movement, and better pulmonary function. However, they did not compare curative effect between modulated-frequency and LF or HF electrical stimulation. Desantana et al. [29] and Pitangui et al. [57] demonstrated that both HF and LF stimulation considerably reduced the intensity of postoperative pain compared to the placebo group. The analgesic effects between the LF and HF group was not compared. However, Oliveira et al. [56] concluded that different frequencies (0 Hz, 7 Hz, 100 Hz and 255 Hz) of electrical stimulation applied to C6–C8 did not show considerable change in the pressure-induced pain threshold or cold-stimulation-induced discomfort in healthy adults. A Cochrane review reported by Walsh et al. [58] in 2011 demonstrated that it is unable to make any definitive conclusions about the effectiveness of electrical stimulation as an isolated treatment for acute pain in adults. Johnson et al. [59] updated this Cochrane review in 2015 by adding another seven studies. They provided preliminary evidence that active electrical stimulation could decrease the acute pain in adults compared to sham electrical stimulation, but this conclusion may come with a high risk of bias because of inappropriate research design. Consistent with previous research, Bjordal [60] found that electrical stimulation notably decreased the demand for postoperative analgesics. However, a system review oppositely demonstrated that HF stimulation was effective in pain control and whether LF stimulation was better than standard care after TKA remains controversial [61]. Another system review obtained an opposite conclusion that the frequency of electrical stimulation had no effect on hypoalgesia [62].

We speculated that inappropriate research design and TEAS parameter selection may explain these controversial conclusions among previous studies. Lack of description of treatment allocation, insufficient blindness control or inappropriate sham method may significantly discount research credibility [59, 63–65]. Besides, inappropriate selection of TEAS parameters may lead to poor quality of the TEAS intervention, thus affecting the efficacy of postoperative acute pain management [61, 65]. Selection of intervention parameters of TEAS is decisive in nonpharmacological therapies [65].

In this study, the research design and selection of TEAS parameters will be modified. The sample size, admission time balance and blinding effect are strictly controlled [35]. In the previous studies aiming to find the optimal frequency, 2 Hz, 4 Hz or 5 Hz were frequently used for investigating the analgesic effect of low frequency, and 80 Hz or 100 Hz were frequently used for investigating the analgesic effect of high frequency [26, 29, 51, 55, 66]. The purpose of this clinical trial is to evaluate the different analgesic effects of low frequency, high frequency and mixed frequency on acute pain after the TKA, rather than evaluating different analgesic effects between different frequency parameter inside the high frequency or low frequency. So we will choose 5 Hz as a representative of low frequency, and 100 Hz as a representative of high frequency. A strong but comfortable current amplitude reported by the participant will be selected to achieve the best analgesic effects [32]. An intervention duration of 30 to 40 min was demanded for the complete expression of pain control effect [33]. The only variable factor of this study is the frequency of TEAS, so the non-research factors which may interfere with the outcomes are well controlled. Thus, stimulation parameters including a strong but comfortable current amplitude, 30-min intervention duration and 200-μs pulse width are consistent in all groups.

Therefore, we hypothesize that the mixed use of TEAS at different frequencies can improve postoperative acute pain, the muscle performance and knee function.

## Abbreviations

AKSS: The American Knee Society Knee Score
ANOVA: Analysis of variance
AROM: Active range of motion
ASA: The American Society of Anesthesiologists
ERAS: The Enhanced Recovery After Surgery
HF: High frequency
iEMG: Integrated electromyography
ITT: Intention-to-treat analysis
KOA: Knee osteoarthritis
LF: Low frequency
m30STS: Modified 30-s sit to stand test
MOR: μ opioid receptor
NRS: Numeric rating scale
OA: Osteoarthritis
OIH: Opioid-induced hyperalgesia
ORSDS: Opioid-Related Symptom Distress Scale
POD: Postoperative day
PP: Per-protocol sets analysis
QoL: Quality of life
RF: Rectus femoris
RMS: Root mean square
SD: Standard deviation
sEMG: Surface electromyography
TEAS: Transcutaneous electrical acupoint stimulation
TENS: Transcutaneous electrical nerve stimulation
TKA: Total knee arthroplasty
VL: Vastus lateralis
VM: Vastus medialis
